**D.3.7 Possible Confounders**

Balance and falls in PD are known to be affected by many factors. Certain medications, such as benzodiazepines, can worsen balance in PD patients.^93^ Depending on the point in their dosing cycle PD severity and dyskinesias (dance-like abnormal involuntary movements) can fluctuate and affect balance. Cognition and a person’s level of physical activity could change over the course of a 4 months study and affect their likelihood of falling.^104^ Therefore, at the baseline and reassessment visit, [name] will administer and record the following assessments:

(1) A medical history: This is to identify the subject’s current medications (subjects will be asked to bring in prescription bottles to every visit) and any new medical issues that could have a significant impact on balance testing (i.e. fracture, stroke). Subjects will be asked to not change any medications during the course of the 16 week study. Specifically patients will be instructed not to start or change doses of amantadine, cholinesterase inhibitors, antidepressants, or benzodiazepines as these may all have significant effects on balance.

(2)PD assessment: The Unified Parkinson's Disease Rating Scale (UPDRS) motor score, a very widely used 30 point scale of severity of PD physical symptoms will be recorded.^105^

(3) Dyskinesia Assessment: This will be measured via a clinical rating scale, the Modified Abnormal Involuntary Movements Score (mAIMS), and an objective measure, the force place dyskinesia rating (see D.5.4).^106, 107^

(4) Cognitive testing: The mini-mental status exam (MMSE) will be used for inclusions and the more in-depth Montreal Cognitive Assessment (MoCA), which has been shown to be sensitive to cognitive deficit in PD, will be used to follow cognitive function at the first and last visit.^109,^ ^110^ In addition the following cognitive tests will be administered: Trail Making A & B, Digit Symbol (WAIS-R), Judgment of Line Orientation, Stroop, Letter-Number Sequencing (WAIS-III), semantic fluency “animals” and “vegetables”, Logical Memory I and II (WMS-R), Boston Naming Test, and Digit Span (WAIS-R).

**D.4.0 Statistical Analysis**

D.4.1 Sample Size: We are basing our power calculation on the primary outcome, the composite SOT (cSOT) score from computerized posturography, for Aim 1. Although we are not assessing power for other outcomes, we will have a reasonable amount of data, targeting 70 subjects per group, to obtain useful information about additional outcomes. Using preliminary data on 20 subjects (see C.4), the average cSOT (SD), excluding one score of zero, was 58.5 (19.1). For conducting a power calculation on the cSOT measure we assume that 10% of subjects will score zero at baseline and follow-up. This is conservative since only 5% of the 20 subjects used for our preliminary data scored zero at a single time point. Among the remaining subjects, we assume SD’s of 19.1 at baseline and follow-up, that the high dose group will have an average score that is 8.8 points higher than at baseline (15% change from 58.5) and the placebo group shows no improvement. There are not studies looking at changes in SOT with vitamin D supplementation, but the Pfeifer did look at body sway, finding a 15% greater improvement in body sway in the intervention versus the control group.^111^  With 10% zeros this 15% change among the non-zeros translates to a mean difference in change of 7.9 points. The SD of the changes from baseline depends on the SD’s at baseline and follow-up and on the correlation between baseline and follow-up measures. We hence obtained sample size requirements using a range of correlation coefficients.

Using simulation with PASS 2008 software, we determined (see Table 7), the sample sizes needed to detect the 7.9 point mean difference indicated above with 80% power at significance level 0.049 (allowing for an interim analysis at significance level .001) for correlations between 0.5 and 0.75. The simulation method was based on the Mann-Whitney nonparametric test which is more conservative in this setting than a t-test procedure (that is, using a simple t-test for the simulation would result in smaller required sample sizes). We will adjust for confounders using parametric methods, but used the non-parametric approach for sample size selection to assure that enough subjects are selected for simple comparisons. The Balance Manager Systems Clinical Interpretation Guide for Computerized Dynamic Posturography report test-retest reliability results ranging from 0.66 to 0.98 for the cSOT.^92^ With 0.66 for correlation, we would require 63 subjects per group. Allowing for 10% drop-out we will then plan to recruit 70 subjects per group.

**Table 7. Sample sizes per group needed for 80% power at significance level 0.049 to detect a mean difference in posturography composite change of 7.9.**

| SD at baseline and at follow-up for composite posturography | Correlation between baseline and follow-up composite posturography | SD of difference between follow-up and baseline scores | Sample size per group |
| --- | --- | --- | --- |
| 19.1 | 0.50 | 19.1 | 91 |
| 19.1 | 0.66 | 15.8 | 63 |
| 19.1 | 0.75 | 13.5 | 47 |

D.4.2 Interim Analysis: When half of the targeted subjects have completed the follow-up visit, we will conduct an interim analysis of the primary outcome using a significance level of 0.001. This was felt appropriate to ensure additional safety for patients. The primary outcome analysis and analysis of other outcomes will be presented to the Data Safety Monitoring Committee, which will be made up of a group of researchers not directly involved in this project. Using a small significance level for the interim analysis requires strong evidence of an effect of Vitamin D for consideration of early stopping (We will use a significance level of 0.049 for the final analysis so that the Type I error rate for the primary outcome remains controlled at 0.05.). The details of the methods used at the interim and/or final analyses are described below.

D.4.3.1 Objective 1 Analysis: The primary analysis will use a Mann-Whitney test to compare the changes from baseline in the cSOT between the placebo and vitamin D groups. We will then use regression methods to adjust for the factors used in randomization, baseline vitamin D level and baseline cSOT, as well as the most important confounders: severity of  motor symptoms of PD (UPDRS motor score) and dyskinesia (clinical dyskinesia scale). With 140 subjects we have more than adequate data to adjust for 4 covariates. Additional covariates that are found to be statistically significant when added to the above model or alter the treatment effect estimate by more than 10% will be included in a second model. In addition to formal tests to compare treatment groups, we will construct 95% confidence intervals for the changes in mean cSOT within each treatment group and for the difference in mean cSOT between treatment groups.

Since Vitamin D serum levels depend on additional factors besides supplementation dose including dietary and sun exposure as well as compliance with study treatment we will perform secondary analyses in which we incorporate serum vitamin D level changes as a covariate in the model allowing us to examine the relationship between cSOT changes and vitamin D level changes.

The use of regression methods assume that residuals follow an approximately normal distribution. If the data do not support this assumption we will consider transformations of the response. If we have more than a few cSOT of zero, we will do a separate analysis of the non-zero scores to determine how this affects our results. We only observed a single cSOT of zero in 20 subjects in our preliminary data, so that we are not anticipating that this will be a significant issue in our study. Also, since we are comparing change from baseline, outliers (other than zero) at a single time point are not likely to result in extreme outliers among the change scores. Hence, other values (besides zero) that are extreme are not expected to have much impact on our results. We will, however, examine the influence of all data points (including outliers) on our conclusions.

We have increased our sample size to accommodate 10% drop-out in our power calculations. However, if subjects dropping out are different from those that do not drop out this introduces bias in our conclusions. If there is more than negligible drop-out we will conduct sensitivity analysis to assess the impact on our results of various assumptions about the reasons for drop-out. Information from participants will be solicited about the reasons for dropping-out to help inform our sensitivity analysis.

The secondary outcome for objective 1 will be analyzed in a similar fashion. For this outcome, root mean square velocity, we will not have the issue of zero scores as we did for the composite posturography measure. The measure of dynamic balance, turn velocity, will also not have the issue of zeros.

D.4.3.2 Objective 2 Analysis: In order to determine if changes in balance are due primarily to changes in strength, we will use regression methods. First we will do analyses similar to above for the static posturography measures (SOT1-SOT3), dynamic posturography measures (SOT4-SOT6), and turn velocity from the iMOBILITY. For the individual dynamic measures, scores of zero will occur more commonly than with the overall composite score and hence we will first compare the proportion of individuals who score zero at baseline, follow-up, and both at baseline and follow-up between the two treatment groups. Descriptive information will be obtained on each of the scores. We will again use the Mann-Whitney test to compare the changes from baseline for each component score between the groups. Composite dynamic and static scores will be obtained by averaging the component scores. The dynamic and static composite scores will be compared using the Mann Whitney test and with regression to adjust for confounders. Again, we expect the composite scores to exhibit few zeros. The influence on our results of zeros (and other data values) will be examined.

We will then compare changes in strength between the two groups using regression methods. We will examine the relationship between changes in strength and changes in the dynamic balance composite score, the static balance composite score, and turn velocity using linear regression methods. The proportions of the variance in the changes in balance and turn duration measures that are explained by the changes in strength will be obtained. In addition to examining the relationship of changes in strength to changes in balance and turn velocity overall, we will examine the relationship after adjustment for treatment group and the confounding variables described above. As in aim 1, we will conduct a secondary analysis to relate changes in outcomes to changes in serum vitamin D.

D.4.3.3 Objective 3 Analysis: For aim 3, we will use the same approaches as above to compare quality of life measures between treatment groups the NHI and the PDQ-39. As a secondary measure to better understand the effect on fear of falling, we will compare the ABC scales between the 2 groups.

D.4.3.4. Additional Analysis: Even though not the primary aim of the study, we feel it would also be useful to look at changes in motor and cognitive function not measured by the gait and balance tests. Therefore we will analyze the UPDRS motor scores and cognitive measures with the same approach as for the other objectives.

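### D.4.1 calls its zero-score assumption conservative, but it is conservative only about how often zeros occur; the stated 80% power also needs every zero to recur at both visits

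*Protocol*

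**What the plan says.** D.4.1 (Sample Size) bases power on the change in cSOT. Pilot data give a mean of 58.5 (SD 19.1) after one zero score is left out. For the trial, "we assume that 10% of subjects will score zero at baseline and follow-up"; the remaining 90% gain 8.8 points on high dose and none on placebo. The defence offered is: "This is conservative since only 5% of the 20 subjects used for our preliminary data scored zero at a single time point".

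The calculation is a simulation ("The simulation method was based on the Mann-Whitney nonparametric test") run "at significance level 0.049 (allowing for an interim analysis at significance level .001"). Its result is "With 0.66 for correlation, we would require 63 subjects per group", raised to 70 for 10% drop-out. The text adds that in this setting the Mann-Whitney test is the more cautious choice, because "using a simple t-test for the simulation would result in smaller required sample sizes".

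Elsewhere, D.4.3.1 plans a separate analysis of non-zero scores if there are more than a few zeros, and excepts zero when it argues that outliers at one visit will not produce extreme change scores. D.4.3.2 plans, for the individual dynamic scores, to compare "the proportion of individuals who score zero at baseline, follow-up, and both at baseline and follow-up".

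**The concern.** The defence compares two different things: 10% of patients at zero on both visits, and 5% of patients at zero on the one visit the pilot had. The first is the larger rate. It is also the pattern that does least harm, because a zero at both visits gives a change of 0, close to the middle of the distribution. A zero at one visit only puts a change of about plus or minus 58 points into a variable whose SD is otherwise about 15.8. The calculation contains no such patient.

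This is the protocol's only power statement. If some zeros are not repeated, a null result would be read against a power the trial did not have, and the conservative label would discourage anyone from asking.

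**Working it through.** **Inputs (D.4.1 and Table 7).** SD 19.1 at each visit; correlation 0.66; mean 58.5; effect 8.8 among non-zeros; two-sided alpha 0.049 (sidedness is not stated, but two-sided reproduces Table 7); 63 per group.

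**Reproducing the plan.** SD of change among non-zeros = 19.1 × √(2 × (1 − 0.66)) = 15.75, printed as 15.8. Mean difference = 0.9 × 8.8 = 7.92, printed as 7.9. Drop-out: 63 / 0.9 = 70. Simulating bivariate normal scores with 10% of patients at zero on both visits, and a tie-corrected Mann-Whitney test on the changes, gives power of 0.80 in all three rows of Table 7 (91, 63 and 47 per group). If the 10% is instead read as an independent rate at each visit, power at 63 per group is only 0.53. So Table 7 rests on full persistence.

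**Why the pattern matters.** With 5% zeros per visit the mean difference is 0.95 × 8.8 = 8.36 whatever the persistence. Only the spread changes. In the placebo group:
- Plan's case, 10% at both visits: SD of change = √(0.90 × 15.75²) = 14.9.
- 5% per visit, independent: 0.95² = 0.9025 have no zero and 2 × 0.05 × 0.95 = 0.095 have exactly one. Variance = 0.9025 × 15.75² + 0.095 × (58.5² + 19.1²) = 223.9 + 359.8 = 583.6, so SD = 24.2.

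**Power by simulation** (20,000 trials per row, 63 per group, same zero rates in both arms). The last column regresses follow-up ranks on baseline ranks and compares the residuals between arms (Quade).

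| Zeros | Whole-score correlation | Mann-Whitney | t-test | Rank test adjusted for baseline |
| --- | --- | --- | --- | --- |
| None | 0.66 | 86% | 87% | 90% |
| Plan: 10%, all at both visits | 0.82 | 80% | 83% | 84% |
| 5% per visit, all persist | 0.77 | 83% | 85% | 87% |
| 5% per visit, 66% persist | 0.65 | 79% | 68% | 82% |
| 5% per visit, half persist | 0.59 | 77% | 61% | 80% |
| 5% per visit, 36% persist | 0.54 | 74% | 56% | 77% |
| 5% per visit, independent | 0.43 | 70% | 47% | 74% |
| 2.5% at each visit, never both | 0.52 | 78% | 63% | 82% |

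Separate runs differ by one to two points. In the last row only 5% of patients ever score zero, half the plan's share, yet power is below the plan's case. With no true effect and independent 5% zeros, the Mann-Whitney and the adjusted rank test reject in about 4.7% and 4.8% of trials, so neither is anti-conservative.

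**If treatment also affects zeros.** Letting the high dose lower the chance of a follow-up zero by a matching latent shift (8.8 / 19.1 = 0.46 SD) gives 82% with independent zeros and 85% with zero status correlated 0.66 on the latent scale.

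**Size in patients.** Under independence at 5%, about 80 evaluable per group are needed for 80% power; 80 / 0.9 gives 89 recruited, against 63 and 70 in the plan.

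**The case against.** The strongest reply is that independence is implausible. The composite draws on six scenarios of three trials each, so a zero marks a patient at the floor and not one bad trial. Testing is at the same time of day for each patient, and medication is to be held constant. D.4.1 cites test-retest reliability of 0.66 to 0.98 for the cSOT; independent 5% zeros pull the whole-score correlation down to 0.43. Holding it near 0.65 gives 78 to 79%, close to the stated figure. This stands, with one reservation: the documents do not show whether the reliability samples contained zeros. It makes 70% the pessimistic end of the range and not the expected value.

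The 5% is itself one patient in 20 (exact 95% interval about 0.1% to 25%), and a treatment that improves balance might move some patients off zero. Both points stand.

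A reader might infer from D.4.3.2 that the plan expects one-visit zeros in the primary outcome. It does not say so: that passage concerns individual dynamic scores and expects few zeros in the composites. A reader might also infer that the t-test remark is false. As written it is confined to the setting simulated, and there it is right (83% against 80%).

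The zero-score analyses in D.4.3.1 and the rank-based primary test limit the damage, but they do not make the power assumption conservative.

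**Conclusion.** The concern holds in a limited form. The label is wrong: the assumption is cautious about the rate of zeros and takes the most favourable pattern for their timing, on which a single pilot visit carries no information. Table 7 is correctly computed for the assumption it makes.

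At 5% zeros per visit, equal in both arms, with correlation 0.66 among non-zeros and 63 evaluable per group, power runs from about 83% (all persist) through 74 to 79% (partial persistence) to about 70% (independent). A reader might conclude that the trial simply has 70% power. The documents do not support that: the figure needs full independence, a rate taken from one patient, and no treatment effect on zeros. If treatment reduces follow-up zeros, power could exceed 80%.

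The t-test loses more than the Mann-Whitney test once zeros occur at one visit (61% against 77% with half persisting). That matters because D.4.3.1 follows the primary test with regression and with confidence intervals for mean cSOT.

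**What to change.** In D.4.1:
- Replace the statement that the assumption is conservative with one saying that the 80% assumes every zero recurs at both visits, which the pilot could not assess.
- Give power as a conditional range over persistence, about 70 to 83% at 5% zeros per visit, naming the other conditions: correlation 0.66 among non-zeros and no treatment effect on zeros.
- Say explicitly that the t-test remark applies to persistent zeros only, and that parametric analyses lose more power when zeros occur at one visit.

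In D.4.3.1, pre-specify the primary comparison as a rank-based analysis of follow-up cSOT adjusted for baseline cSOT, which is already measured and which that section lists among the randomization factors. It gives about 84 to 85% against 80% in the plan's own case, and 74 to 76% against 70 to 71% with independent 5% zeros.

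The cost is wording, a less favourable stated power, and a change to the declared primary test, which should be made before any unblinded look, including the planned interim analysis. No extra patients, visits or measurements are needed. If the primary test is left as it is, the D.4.1 corrections are still needed.

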**B.4 Vitamin D and Parkinson’s disease**

Vitamin D deficiency is prevalent in PD. Our data from the MrOS study found that 21% of the men with PD were deficient and another 50% were insufficient in vitamin D.^4^ Vitamin D deficiency is more common in PD than in AD. In the Atlanta area 55% of persons with PD had insufficient vitamin D levels as compared to 41% of persons with AD.^78^ Vitamin D deficiency seems particularly prevalent later in disease, with rates as high as 78%.^79^ This is precisely when balance problems are most prominent. It is not entirely clear if vitamin D metabolism is unique in persons with PD, but deficiency is clearly prevalent.

A central mechanism through which vitamin D could affect balance in elderly fallers is not well understood. The presence of vitamin D receptors and the final converting enzyme in vitamin D metabolism in the brain suggests a role in CNS function. The beneficial effects of vitamin D may be a general effect on neurons through its up-regulation of neurotrophic factors such as GDNF.^80, 81^ In terms of the regions postulated to be responsible for the gait and balance problems in PD, animal studies show protection of the locus coeruleus (with a predominance of noradrenergic neurons) by systemic vitamin D which attenuated iron-induced oxidative injuries in rats.^82^ In cortical cell cultures, vitamin D pretreatment decreased cyanide-induced cell death which seemed to be through up regulation of UCP-2 (uncoupling protein-2) resulting in reduced mitochondrial protein leak and stabilization of mitochondrial function.^83^ Other cell population may be similar, but are not yet been studied or reported in the literature. The Ibi study found protective effect from subsequent insult was only present when vitamin D was given at least 8 hours prior to the toxic insult, suggesting protein synthesis is required.^84^ The particularly high prevalence of vitamin D receptors in the substantia nigra (likely on dopamine cells) the primarily area of pathology in PD is of obvious interest. Eyles et. al. found vitamin D receptors were present in 42 brain areas but only stained at the highest level within the substantia nigra.^22^ Even though the dopaminergic system may not be responsible for balance problems in PD, it is possible vitamin D has affects on motor symptoms such as tremor, rigidity, and slowness.

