**Table 4: Detailed time line**

| **Year of grant (date)** | **Activities** | **# of subjects completed** |
| --- | --- | --- |
| 1 (July 2010-2011) | IRB approval  Animal research project  Recruitment  Begin data collection | 40 |
| 2 (July2011-2012) | Data collection | 80 |
| 3 (July 2012-2013) | Data collection | 120 |
| 4 (July 2013-2014) | Data collection  Analysis of baseline data | 140 |
| 5 (July 2014-2015) | Data analysis  Manuscript Preparation | 140 |

Randomization: We will use a permuted block randomization scheme to allocate treatments using strata determined by two factors: baseline vitamin D levels (>20-<30 vs. >30-<40ng/ml) and baseline composite SOT4-6 ( <64 vs. >64). This is based on what is considered insufficiency of vitamin D and the mean normative SOT score for persons 70-79 years old respectively.^59, 92^ Those with < 20 ng/ml baseline vitamin D levels will be enrolled into the vitamin D supplementation arm and will receive 10,000 IU of vitamin D for 16 weeks in an open label fashion. Those with > 40 ng/ml at baseline will not be enrolled in this study.

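### The second regression model for cSOT chooses its covariates by significance or a 10% shift in the treatment estimate, and the adjustment covariates are not all tied to baseline values

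*Protocol*

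**What the plan says.** Protocol D.4.3.1 sets out three layers for the composite SOT score (cSOT).

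1. **Primary test.** "The primary analysis will use a Mann-Whitney test to compare the changes from baseline in the cSOT" between the two arms, unadjusted.
2. **First regression.** Treatment plus four named covariates: baseline vitamin D, baseline cSOT, UPDRS motor score and the clinical dyskinesia scale. The sample is called sufficient for this: "With 140 subjects we have more than adequate data to adjust for 4 covariates".
3. **Second regression.** "Additional covariates that are found to be statistically significant when added to the above model", or that "alter the treatment effect estimate by more than 10% will be included in a second model". The candidates are not listed.

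The word baseline is attached to vitamin D and cSOT only. D.3.7 says that the possible confounders (medical history and medications, UPDRS motor score, dyskinesia, cognition) are recorded "at the baseline and reassessment visit". Table 5 lists medications, cognition, UPDRS and dyskinesia under the confounder heading again at Visit 5.

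Some of these variables are also outcomes. D.4.3.4 states that "we will analyze the UPDRS motor scores and cognitive measures with the same approach as for the other objectives", and B.4 says "it is possible vitamin D has affects on motor symptoms such as tremor, rigidity, and slowness".

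Sections D.4.3.1 to D.4.3.4 carry the same approach to the other balance, quality-of-life, motor and cognitive outcomes.

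**The concern.** A change-in-estimate rule is a tool for confounding in observational data. Here allocation is randomised (D.2: "We will use a permuted block randomization scheme to allocate treatments using strata determined by two factors"), so a baseline covariate can move the treatment estimate only through chance imbalance. Choosing covariates because they move the estimate means choosing them by their effect on the answer. The threshold is also relative: 10% of a small estimate is a very small number of points, so the rule is loosest when the observed effect is modest or absent. That is when readers are most likely to turn to adjusted results.

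Timing is a second matter. If a 16-week value of UPDRS, dyskinesia or cognition enters a model, and vitamin D has changed that value, part of the treatment effect is adjusted away. The 10% criterion would tend to admit such a variable, because a variable that carries part of the effect is one that moves the estimate.

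At stake are the content and interpretation of the adjusted estimates, for cSOT and for every outcome analysed the same way.

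**Working it through.** **Inputs from the protocol (D.4.1, D.4.2, Table 7).** SD 19.1 at each visit, correlation 0.66, design effect 7.9 points, final significance level 0.049, power 80%, 63 per group before drop-out.

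**Assumed inputs.** Two-sided tests; 0.05 as the covariate selection threshold (none is stated); 5, 10 or 15 candidates, tested one at a time; candidates unrelated to outcome and treatment.

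**Step 1: reproduce the plan's setting.**
- SD of change = 19.1 × √(2 × (1 − 0.66)) = 15.75 (Table 7: 15.8).
- n per group = 2 × (1.969 + 0.842)² × SD² / 7.9² = 15.79 × 15.75² / 7.9² = 62.8, so 63, as stated.
- 63 / 0.90 = 70, as stated.
- The same formula gives 93 and 47 for correlations 0.50 and 0.75 (Table 7: 91 and 47). The plan's figures come from a Mann-Whitney simulation; repeating one gives about 80% power at each stated n.

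The sample size is not in dispute. It supplies the setting for the next steps.

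**Step 2: how far a noise covariate moves the estimate.** The shift is roughly the covariate's fitted slope times its imbalance between arms.
- SD of slope: 15.75 / √126 = 1.40.
- SD of imbalance: √(2/63) = 0.178.
- Typical shift: 1.40 × 0.178 = 0.25 points, multiplied by the product of two independent standard normal variables.
- Standard error of the treatment estimate: 15.75 × √(2/63) = 2.81.

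At an estimate of 7.9 the 10% threshold is 0.79 points, about three times the typical shift. At zero true effect the median absolute estimate is about 0.674 × 2.81 = 1.9, so the threshold is about 0.19 points, below the typical shift. This approximation gives pass rates of 35%, 18% and 4% at effects of 0, 4 and 7.9 points.

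**Step 3: full simulation** (3,000 trials per setting, 63 per group, treatment plus four covariates as the first model).

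Chance that one pure-noise candidate is selected:

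| True effect | 10% criterion | Significance | Either |
|---|---|---|---|
| 0 | 35% | 5% | 37% |
| 4.0 | 19% | 5% | 22% |
| 7.9 | 4% | 5% | 8% |

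Chance that at least one noise candidate enters by the full rule:

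| True effect | 5 candidates | 10 candidates | 15 candidates |
|---|---|---|---|
| 0 | 78% | 92% | 95% |
| 4.0 | 59% | 76% | 84% |
| 7.9 | 32% | 54% | 64% |

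**Step 4: type I error in the second model.** Tested at 5%, the treatment term rejects in 5.2%, 5.4% and 6.5% of null trials with 5, 10 and 15 candidates. The first model gives 4.8%, 4.6% and 5.3% in the same runs. The simulation error of each rate is about √(0.05 × 0.95 / 3,000) = 0.4 percentage points. Testing at 0.049 instead would change little.

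**Step 5: a treatment-affected covariate (illustration only).** If a follow-up covariate carries a share s of a 7.9-point effect, full adjustment leaves 7.9 × (1 − s): 7.1, 5.9 and 4.0 points (3.95 before rounding) for s = 10%, 25% and 50%. Assume treatment also shifts that covariate by 0.5 SD. The rule then selects it in 51%, 92% and 100% of simulated trials, and the mean estimate after applying the rule is 7.2, 6.0 and 4.0. No document gives a value for s or for the 0.5 SD shift.

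**The case against.** Four points can be made for the plan.

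- **The rule sits low in the hierarchy.** It governs a supportive model that comes after a prespecified test and a prespecified regression. This stands. A reader might infer that the trial's main conclusion has an inflated false-positive rate; the protocol does not support that, because the type I error control in D.4.2 is for the primary outcome and the Mann-Whitney test uses no covariates. Nor is the rule harmful at the design effect, where a noise covariate passes the 10% criterion slightly less often than a 5% significance test.
- **The rule also finds useful covariates.** This is true. With five covariates each correlated 0.3 with the outcome, each is selected 93% of the time and power rises from 79% to 96%. But prognostic baseline covariates can be named in advance, which gives the gain without the search.
- **Follow-up adjustment is read into silence.** A reader might infer that the plan will adjust for 16-week values; no sentence says so. Where D.4.3.1 and D.4.3.2 want a change as a covariate (serum vitamin D, strength), they say so. Follow-up UPDRS and cognition are needed as outcomes anyway. What remains is an ambiguity: D.3.7 and Table 5 label the reassessment measures as confounders, and no timing is given.
- **Candidates and timing can be left to an SAP.** A list can. The selection rule itself is fixed in the protocol and would remain.

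D.5.4 also gives a measurement reason to look at dyskinesia at testing, since it may register as poor balance. That supports a separate exploratory analysis, not an unspecified place in the adjusted model.

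**Conclusion.** The concern holds for the supportive adjusted analyses. The rule makes the second model's content largely accidental when the effect is small: about 35% of pure-noise candidates pass the 10% criterion at zero effect, 19% at 4 points and 4% at 7.9. With 5 to 15 candidates, at least one enters in 78% to 95% of null trials. The cost in type I error is small, at most about 6.5% in the settings run. The main fault is an adjusted estimate whose specification depends on the data.

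The timing gap is real but conditional. It also touches two of the four terms in the first regression, UPDRS motor score and dyskinesia. If treatment-affected values were used, the estimate would move towards zero by the share of the benefit they carry. That share is unknown, so the figures in step 5 illustrate a mechanism and do not estimate a bias in this trial.

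The results rest on the assumed number of candidates, independent noise covariates, a 0.05 selection threshold and two-sided testing.

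**What to change.** In D.4.3.1:

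- Delete the significance and 10% criteria.
- Keep the four-covariate regression as the adjusted analysis. Name any further prognostic baseline covariates before unblinding.
- State that UPDRS motor score, dyskinesia and all other adjustment covariates are pre-randomisation values, and that this applies to Objectives 1 to 3 and the additional analyses.
- Report follow-up UPDRS, dyskinesia, cognition and medication changes by arm, or use them only in analyses labelled exploratory. The serum vitamin D and strength-change analyses are already set out separately and can stay as they are.

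The cost is analysis wording only, with no change to design, sample size or data collection. The one downside is that a prognostic covariate nobody named in advance will not be picked up.
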